### Data Analysis

#### Quantitative Data

To ensure analytical independence, all quantitative data extraction and cleaning will be performed exclusively by an independent research officer, who has no affiliation with In2Health Solutions. The PhD candidate will not access any study dataset until the statistical analysis plan (SAP) has been finalized, independently reviewed, and approved by the supervisors (HH, EH, and AB). The SAP will be preregistered and archived on the Open Science Framework prior to data extraction. Analyses will be conducted by the PhD candidate and independently verified by the research officer, with academic oversight provided by the supervision team. All analytical code will be version-controlled, and the SAP will contain the IBM SPSS (Statistical Package for Social Sciences) syntax for multilevel regression models, missing data procedures, and sensitivity analyses.

#### Primary Outcome Analyses (Feasibility End Points)

Descriptive statistics will be calculated for all variables, including frequencies for categorical data and means or medians for continuous variables. Engagement levels will be examined in relation to participant characteristics using nonparametric methods, including the Kruskal-Wallis *H* test and the Spearman rank correlation. Acceptability scores will be summarized for each domain of the UTAUT2 [49,98] and compared between user subgroups.

The proportion and patterns of missing baseline and follow-up data will be documented as part of the feasibility assessment. Given the descriptive nature of feasibility end points, no imputation will be undertaken. For baseline acceptability data, incomplete responses will be excluded from domain-level mean score calculations using listwise deletion [105]. Missing usage log data will be interpreted as nonengagement rather than missingness.

As a secondary exploratory analysis, multilevel logistic regression models will be used to examine predictors of engagement, with practice included as a random intercept to account for clustering.

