### Sample Size

#### Consumer Participants

As a feasibility study, this trial is not powered to detect statistically significant differences in outcomes. Instead, the sample size was determined to allow for the estimation of key feasibility indicators with acceptable precision [52]. If approximately 50% of participants who consent complete the THRIVE health assessment, with a 10% margin of error at a 95% CI, a minimum sample size of 187 consumers will be required.

In line with previous general practice research [53-57], a cluster adjustment was applied to the sample calculation using an intracluster correlation coefficient of 0.05 [53-57]. With an anticipated 5 participating practices and a design effect of 1.95, allowing for an estimated 15% dropout rate, the adjusted sample size requirement will be 215 consumers. Therefore, each practice is expected to recruit at least 43 participants.

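### First-line tests of what relates to engagement pool consumers across practices, while the practice-adjusted model of the same question is ranked below them

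*Protocol article*

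**What the plan says.** The first primary objective of the Protocol article is to examine what influences engagement by clinicians and consumers. For consumers, the section Primary Outcome Analyses (Feasibility End Points) puts rank tests first: "Engagement levels will be examined in relation to participant characteristics using nonparametric methods, including the Kruskal-Wallis" "test and the Spearman rank correlation". That sentence does not mention practice.

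The same section then returns to the question with a clustered model at a lower rank: "As a secondary exploratory analysis, multilevel logistic regression models will be used to examine predictors of engagement, with practice included as a random intercept".

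The sample size section assumes that consumers of one practice resemble each other: "a cluster adjustment was applied to the sample calculation using an intracluster correlation coefficient of 0.05". It continues: "With an anticipated 5 participating practices and a design effect of 1.95, allowing for an estimated 15% dropout rate". The Settings section has practices chosen to differ in location (metropolitan, regional, rural), across three states. The covariates listed under Secondary Outcome Analyses include education, employment and postcode as a socioeconomic indicator.

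**The concern.** Kruskal-Wallis and Spearman p values are valid when observations are independent. If engagement and a characteristic both vary by practice, a chance difference in engagement between five sites can appear as an association with that characteristic. The p value is then too small. The coefficient itself also blends two things: how consumers differ within a practice, and how the practices differ from one another.

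Engagement could well vary by site, because recruitment and encouragement run through the practice (posters, newsletters where available, optional prompting by clinicians). Some characteristics, postcode above all, could vary by site too. Engagement findings are meant to guide refinement of THRIVE, so a site difference taken for a consumer difference could point that work the wrong way. The article does not say which result prevails if the rank tests and the multilevel model disagree.

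**Working it through.** **1. The plan's own clustering figures.** Inputs from the sample size section: "If approximately 50% of participants who consent complete the THRIVE health assessment, with a 10% margin of error at a 95% CI"; ICC 0.05; design effect 1.95; 15% dropout; 5 practices.

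- Unclustered: 1.96² × 0.5 × 0.5 / 0.10² = 96.04.
- With the design effect: 96.04 × 1.95 = 187.3 (stated 187).
- With dropout: 187 × 1.15 = 215.05 (stated 215), and 215 / 5 = 43 per practice, as in "each practice is expected to recruit at least 43 participants".

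The figures reproduce. A design effect of 1.95 equals 1 + (20 − 1) × 0.05, which corresponds to about 20 consumers per practice. I use m = 43, the stated recruitment, and give m = 20 as a lower case.

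**2. Approximate error rate.** When outcome and characteristic both cluster, the variance of a pooled association is inflated by about DE = 1 + (m − 1) × ICC_y × ICC_x. A nominal two-sided 5% test then rejects with probability 2 × [1 − Φ(1.96/√DE)]. With ICC_y = 0.05 and m = 43:

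- ICC_x = 0: DE = 1.00, error 5.0%.
- ICC_x = 0.2: DE = 1 + 42 × 0.05 × 0.2 = 1.42, 1.96/√1.42 = 1.645, error 10.0%.
- ICC_x = 0.5: DE = 2.05, 1.96/√2.05 = 1.369, error 17.1%.

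With m = 20, the results at ICC_x = 0.2 and 0.5 are DE = 1.19 (7.2%) and DE = 1.475 (10.7%).

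**3. Simulation of the named tests.** The formula is rough for ordered levels and only five practices, so the tests were also simulated. The settings were 5 × 43 consumers, latent engagement ICC 0.05, five ordered levels with half of consumers in the lowest, no true association, and 4,000 runs per setting. The Monte Carlo standard error near 5% is √(0.05 × 0.95 / 4000), about 0.3 points. Percentage of runs with p < 0.05:

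| Characteristic ICC (assumed) | Spearman, pooled | Kruskal-Wallis, engagement by thirds of the characteristic | Kruskal-Wallis, characteristic across five engagement levels | Spearman, ranks centred within practice |
|---|---|---|---|---|
| 0 | 4.8 | 5.1 | 4.8 | 4.7 |
| 0.05 | 5.6 | 5.1 | 5.0 | 5.1 |
| 0.1 | 6.1 | 5.1 | 5.4 | 4.8 |
| 0.2 | 7.6 | 6.1 | 5.9 | 4.6 |
| 0.5 | 12.6 | 10.8 | 8.6 | 4.7 |
| 1 (constant within practice) | 23.3 | 27.8 | 15.1 | not testable |

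A further run at a characteristic ICC of 0.8 gave about 18% for pooled Spearman and about 5% after within-practice ranking.

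**4. Reading the table.** There is no inflation when the characteristic does not cluster, and little up to an ICC of 0.1. It becomes material from about 0.2 for Spearman and somewhat higher for Kruskal-Wallis. Ranking within practice restores the nominal level wherever it can be applied.

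**The case against.** The case for leaving the plan alone has real weight.

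- **The clustered model is already there.** It stands in the same section, addresses the same question and carries a random practice intercept. A covariate set for exploratory analysis of engagement predictors is fixed in advance. A reader might infer that the plan ignores clustering for engagement, or that site effects will inevitably be reported as consumer effects. The article does not support either reading.
- **Formal error rates carry little weight here.** No significance level is stated, the study is expressly not powered for significance, and feasibility end points are called descriptive. Correlates of engagement are not a progression criterion, so a reader should not infer that the decision to proceed is at risk. Interviews also inform the same objective.
- **The size rests on assumed ICCs.** The article gives none for characteristics. Postcode is the clearest candidate for a high value; nothing in the article suggests one for age, gender or activation.

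All of this stands, and it lowers the importance of the point. It does not remove it. The remark about description is the reason given for not imputing, and it leaves two named tests in place. The explicit waiver of significance interpretation sits under Secondary Outcome Analyses and covers activation, self-rated health and risk scores. Nor is this a detail left to the SAP, since the article itself names the tests and ranks the clustered model beneath them. Calling a pooled association descriptive does not separate its within-practice from its between-practice part.

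**Conclusion.** The point holds in a limited form. The first-line analysis of consumer engagement correlates ignores the clustering that the study's own sample size assumes, and the analysis that respects it is ranked second. The consequence is confined to characteristics that differ by practice. For those, a nominal 5% Spearman test errs at about 8%, 12% and 18% for characteristic ICCs of 0.2, 0.5 and 0.8. Kruskal-Wallis errs at about 6% at 0.2 and about 9% to 11% at 0.5, according to how it is applied.

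These figures assume 43 consumers in each of five practices, that the ICC of 0.05 carries over to the engagement levels, half of consumers in the lowest level, and a 5% test. The characteristic ICCs are assumptions throughout. With about 20 per practice the excess is smaller.

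The rates of 15% to 28% apply only to traits that are constant within a practice, and should not be read as typical of the planned analyses. This is a cheap improvement to the order and reporting of analyses, not a defect that undermines the feasibility conclusions.

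**What to change.** The simplest change is to state in the SAP that the planned multilevel model with practice is the main analysis of consumer engagement predictors. The pooled Kruskal-Wallis and Spearman results would then be reported descriptively, without p values. The SAP should also say how the five engagement levels enter the logistic model.

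Alternatively, keep rank methods as the lead but apply them within practice: a practice-stratified k-group version of Kruskal-Wallis (the van Elteren test serves only for two groups), and a within-practice Spearman correlation or a permutation test that shuffles within practice.

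Under either route, label characteristics that vary mainly between the five practices as descriptive only. Five sites give little information on them under any method, including the random-intercept model.

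The cost is some SAP wording and a little syntax. The article says the SAP will be registered before data extraction, with follow-up expected to end in December 2026, so the change fits that sequence. The downside is little power for characteristics that hardly vary within a practice.

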#### Consumer Data Collection

Quantitative data will be collected via self-administered online surveys at baseline and 6 months post enrollment. These surveys will assess outcomes related to acceptability, engagement, and early indicators of effectiveness, including activation and self-rated health. The estimated total time commitment for consumer participants is 75 minutes over 6 months, including participation in surveys, digital assessments, and optional interviews.

Engagement data will be passively collected through the THRIVE platform, including metrics such as login frequency, dashboard views, goal setting, action plan access, and responses to health reminder prompts. Following the postintervention survey, participants will be invited to opt-in to subsequent interviews by providing their contact details. As part of this process, participants will self-report their level of intervention engagement (eg, high, medium, low, or none), to guide sampling stratification. This process ensures that codified (controlled) and identifiable (protected) data are handled separately.

Approximately 18 to 20 consumer interviews (up to 4 per clinic) will be conducted via videoconference, audio-recorded, transcribed verbatim, and complemented by researcher field notes. A qualitative descriptive approach will be used to explore perceptions of intervention acceptability, sustainability, impact, and opportunities for improvement. Final numbers will be guided by data sufficiency. The semistructured interview guide is included in Multimedia Appendix 1 [66,68-91].

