#### Engagement

Engagement will be measured using THRIVE usage logs, which automatically record participants’ interactions with the platform. Based on these behaviors over the 6-month study period, participants will be classified into 1 of 5 engagement levels (Figure 2). Individuals who consent but do not initiate or complete the risk assessment will be classified within the “no use” engagement category. This group will be included in follow-up surveys and purposive qualitative sampling to capture barriers to engagement.

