#### Acceptability

Consumer acceptability will be assessed in the postintervention survey using items from 8 of the UTAUT2 domains: performance expectancy, effort expectancy, social influence, facilitating conditions, hedonic motivation, trust, habit, and behavioral intention Multimedia Appendix 1 [66,68-91] [49,50,93,98]. The UTAUT2 has been widely applied to evaluate the adoption of consumer-facing technologies [50,93,99,100]. It has demonstrated strong internal consistency (Cronbach α range=0.637‐0.902 across domains) [93] and high reliability to evaluate acceptability (range ⍺=0.837‐0.899) [95]

Items are rated on a 7-point Likert scale, from 1 (“strongly disagree”) to 7 (“strongly agree”), with higher scores indicating greater acceptability. Six questions across 5 domains are shared between the 2 groups, with additional questions tailored to context-specific relevance depending on engagement levels. For example, in the performance expectancy domain, users respond to “I found the THRIVE program to be useful,” while nonusers respond to “I know what to do to stay healthy so I didn’t need this program.”

User participants will complete 18 items across the 8 UTAUT2 domains. Acceptability outcomes will be reported using the following 2 complementary metrics [51]: (1) the mean acceptability score across domains with scores of more than 4 considered indicative of acceptability (ie, responses in the “somewhat agree” to “strongly agree” range) and (2) the proportion of participants whose individual mean scores meet or exceed the threshold, with 70% or more representing a benchmark for acceptable uptake. Together, these metrics provide insights into both the overall perceived acceptability and the consistency of this perception across participants.

Nonuser participants will complete 12 items across 7 relevant domains (excluding “habit,” which is not applicable to those who did not engage with the intervention). The primary purpose of this analysis is to explore the domain-specific barriers to acceptability. First, item-level responses of more than 4 will be interpreted as indicating a potential concern within a specific domain. Second, we will report the proportion of nonusers whose mean domain scores are more than 4 to reflect broader patterns of perceived difficulty or lack of relevance.

These acceptability thresholds align with typical group-level acceptability criteria in other digital health evaluations [101,102] and were established a priori (Table 2).

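### The acceptability missing-data rule names baseline data that are never collected, and the 70% benchmark measures acceptability among responding assessment completers, not uptake

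*Protocol article*

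**What the plan says.** **Timing.** The Acceptability section states: "Consumer acceptability will be assessed in the postintervention survey using items from 8 of the UTAUT2 domains". Table 1 also lists acceptability as postintervention. Under Consumer Data Collection, "Quantitative data will be collected via self-administered online surveys at baseline and 6 months post enrollment".

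**Who is scored.** Under Engagement, "Individuals who consent but do not initiate or complete the risk assessment will be classified within the" no-use category, and "This group will be included in follow-up surveys and purposive qualitative sampling to capture barriers to engagement". Under Acceptability, "User participants will complete 18 items across the 8 UTAUT2 domains". Nonusers answer 12 items, some worded differently, on which high scores signal a barrier and not acceptance.

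**Benchmark.** One of the two user metrics is "the proportion of participants whose individual mean scores meet or exceed the threshold, with 70% or more representing a benchmark for acceptable uptake".

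**Missing data.** Primary Outcome Analyses rules out imputation for the feasibility end points and then says: "For baseline acceptability data, incomplete responses will be excluded from domain-level mean score calculations using listwise deletion". It adds: "Missing usage log data will be interpreted as nonengagement rather than missingness". The extent and pattern of missing data are to be documented.

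**Use.** Under Progression Criteria, the most favourable outcome requires the feasibility indicators to reach their thresholds and the qualitative findings to be supportive.

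**The concern.** There are two faults in what is written.

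First, the listwise-deletion rule is attached to data that will not exist. Partly completed postintervention acceptability surveys, which will exist, are left without a stated rule.

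Second, the 70% figure is conditional on two steps, finishing the assessment and returning the 6-month survey. The protocol expects about half of consenters to fail the first step. A percentage taken after both steps describes how acceptable THRIVE is to those who remain. It cannot say how many people took it up. A reader of the progression assessment who sees 70% labelled as acceptable uptake could take it to apply to consenters, or at least to all users.

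The no-use category also joins people who never opened the assessment with people who began and stopped. For a feasibility study these point to different problems: access or interest in one case, the burden of the assessment in the other.

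The denominator matters because acceptability is the only consumer feasibility component to which the text attaches a numeric threshold. The figure that defines the engagement levels is not in the copy reviewed.

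**Working it through.** **1. Is there any baseline acceptability measure?** The Outcomes section places sociodemographics, perceived disease threat and trust in the therapeutic relationship in the baseline survey. Activation and self-rated health are also measured preintervention. The nearest candidate is the set of four perceived-threat items, which come from UTAUT2. They are covariates, and perceived threat is not among the eight acceptability domains in Table 2. No baseline acceptability score is planned, so the rule has no object.

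**2. Reproducing the protocol's sample size.** Inputs from Sample Size: proportion 0.50, margin 0.10, 95% confidence, design effect 1.95, dropout 15%.
- 1.96² × 0.5 × 0.5 / 0.10² = 96.04
- 96.04 × 1.95 = 187.3 (stated: 187)
- 187 × 1.15 = 215.05 (stated: 215)

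The figure of 215 reproduces and is the starting point below.

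**3. Who is in the 70%.** Users are taken to be assessment completers, because everyone who does not start or does not finish is classed as no use. The 15% loss is assumed equal in users and nonusers.
- Users: 215 × 0.50 = 107.5
- Responding users: 107.5 × 0.85 = 91.4, about 91
- Needed to meet the benchmark: 0.70 × 91.4 = 64.0
- As a share of all users, if no nonresponding user accepts: 64.0 / 107.5 = 59.5%
- As a share of consenters: 64 / 215 = 29.8%

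If completion were 40% or 60% (assumed range), the share of consenters would be 0.40 × 0.85 × 0.70 = 23.8% or 0.60 × 0.85 × 0.70 = 35.7%.

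**4. How far nonresponse could move the figure.** Let d be the loss among users and q the acceptance rate among nonresponding users. If responders sit exactly at 70%, the rate among all users is 0.70 × (1 − d) + q × d.

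| Loss d | q = 0% | q = 30% | q = 50% | q = 70% | q = 90% |
|---|---|---|---|---|---|
| 15% (protocol) | 59.5% | 64.0% | 67.0% | 70.0% | 73.0% |
| 30% (assumed) | 49.0% | 58.0% | 64.0% | 70.0% | 76.0% |
| 50% (assumed) | 35.0% | 50.0% | 60.0% | 70.0% | 80.0% |

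At 15% loss, 70% of all users is guaranteed only if the rate among responders is at least 0.70 / 0.85 = 82.4%.

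**The case against.** The strongest reply is that only one word is wrong and everything else is handled or is a matter of preference. Much of that stands.

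- **Direction of bias.** A reader might infer that the plan pushes the progression decision upward. The documents do not show this. The figure is too high only if nonresponding users are less favourable than responders. At 15% loss the table runs from 10.5 points too high (q = 0%) to 3 points too low (q = 90%). The misplaced word creates no bias itself.
- **Other inputs to the decision.** The progression framework is explicitly flexible. Engagement is a separate primary component in which those who did not finish count as no use, and qualitative findings must also be supportive. Counting missing logs as nonengagement lowers measured engagement, so it cannot simply be read as favouring progression. The text also does not say whether logs or self-reported engagement decide which survey version a person receives.
- **People who stop midway.** A reader might want them in the main user denominator. They have not seen the dashboard or action plan, which follow completion. Scoring them as not accepting would mix uptake with acceptability among those exposed. That is a debatable change of the quantity being estimated, and the documents do not call for it.
- **Nonuser barriers.** Nonusers are surveyed and sampled for interview, and their items cover effort and facilitating conditions.
- **The analysis plan.** Avoiding imputation for a descriptive end point is defensible. The SAP, not shown, is to contain missing-data procedures and sensitivity analyses, so their absence from the article is not a fault.

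None of this gives the listwise rule data to act on. It does not make a rate among responding completers a measure of uptake, and it does not separate never-started from started-not-completed participants.

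**Conclusion.** The point holds in limited form. The listwise rule contradicts the stated timing of the acceptability measure and must be corrected; this rests on the text alone. The 70% benchmark is acceptability among assessment completers who return the 6-month survey, and calling it uptake is wrong.

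Under the protocol's 50% completion and 15% dropout, with equal loss in users and nonusers assumed, just meeting the benchmark means about 64 of 91 responders. That is compatible with 59.5% to 73.0% of all users for nonresponder acceptance of 0% to 90%. The corresponding 29.8% of consenters answers a different question from acceptability among users and is not a measure of bias, but it shows how far the benchmark is from uptake. Overstatement among users is possible, not demonstrated.

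**What to change.** 1. In Primary Outcome Analyses, change *baseline* to *postintervention* in the listwise-deletion rule.
2. In Acceptability, describe the 70% figure as acceptability among responding users and remove the reference to uptake.
3. Report it beside the 6-month survey response rate among users, with a sensitivity result that counts nonresponding users as not meeting the threshold. Quote both results in the progression assessment.
4. Use the platform logs to report never-started and started-not-completed participants separately within no use, leaving the main user denominator as it is.

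The cost is a wording change, one extra table and a possibly less favourable figure. No new data are needed. The SAP is to be preregistered before data extraction, so the changes can be fixed there before anyone has seen the results.
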